## Abstract

Background: Although mortality rates have declined in Uganda over the last decade, maternal mortality is still high at 336 deaths per 100,000 live births, as is infant mortality at 43 deaths per 1000 live births. One in every 19 babies born in Uganda does not live to celebrate their first birthday. Many of these deaths occur within the first 28 days of life, forming the single largest category of death. Promising effects for preventing death are expected from timed and targeted counselling (ttC), an intervention package of key messages and actions that address integrated health and nutrition needs of the mothers and children, barriers and negotiation agreement, to cause sustainable behavioural change at specific timelines in the first 1000 days. Methods: The study has a quasi-experimental design in order to evaluate the implementation and effectiveness of the ttC intervention. Participants are pregnant women who have been registered by village health team (VHT) members and who live in Hoima (intervention region) or Masindi (control region) districts, who will be monitored throughout their pregnancy up to at least six weeks after delivery. A multi-stage sampling technique will be employed to select participants, the study sites being purposively chosen. Sample size is determined using the pregnancy rate from the population estimates, resulting in a total required sample of 1218 (609 each in the intervention and control group). Study instruments that will be used include the Ugandan VHT household register (in which all mothers to be studied will be registered), the ttC register (an additional tool for the study area), and a study questionnaire, to collect data at outcome level. Univariate, bivariate and multivariate analyses will be performed using SPSS to evaluate intervention effects on outcomes (e.g., relationship between pregnancy outcomes and antenatal attendance). In addition, quantitative findings will be triangulated with qualitative data, and collected through interviews and focus group discussions with participants and implementers. Discussion: The proposed study will examine the effectiveness of implementing ttC to improve maternal and child outcomes in Uganda. If ttC is effective, broader implementation of appropriate antenatal services can be advised as essential newborn care improvements. Trial registration: PACTR, PACTR202002812123868. Registered on 25 February 2020.

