### 2.4. Study Population

The study population for the quantitative study involves pregnant mothers registered by VHTs on suspecting the pregnancy. The study will follow these participants from pregnancy until six weeks post-delivery. For qualitative data (key informant interviews and focus group discussions), mothers shall be enrolled towards the end of the study period. Enrolment for the qualitative process evaluation will also cover VHTs, health facility staff, district health leaders and staff from the World Vision Uganda office in the department of health. To be included, women have to have either an ANC card with a child health card or a mother-child passport. Participants shall be considered discontinued if they migrate from the location included into the study at any point in time during the community health worker (CHW) follow up period.

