The ttC visits are at given times in the first 1000 days window to pass on a given message, to trigger the household to support the mother to go for a given service at the health centre. The visits that the VHT makes are in line with the Ministry of Health (MoH) goal-oriented ANC [21] services package, the institutional delivery framework of the road to the reduction of maternal and newborn death in Uganda [22] including the essential newborn care at the facility and the community level. For this study, our focus is on the value of the four visits made during pregnancy, the three visits made when the child is in the newborn period for essential newborn care practices and a fourth visit at six weeks to enhance exclusive breastfeeding and routine immunization. The CHWs are convened by the sub county assistant on a monthly basis to ensure they adhere to the household visits and note each action in the ttC household register. The visits are specified in Table 1.

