**Figure 3 mps-03-00073-f003:**
[figure not shown]
The sampling flow framework.

**Table 1 mps-03-00073-t001:** Timed and targeted counselling (ttC) visits by village health teams (VHTs) to mothers during pregnancy or after childbirth.

Visit	Timing	Services Delivered by the VHTs
1	Before or at 3 months	Focuses on suspected pregnant mothers registered as ttC candidates. They are counselled on how to care for themselves during pregnancy, a list of danger signs during pregnancy is explained, and the family is encouraged to notify the VHT in the case of any of these danger signs. Families are counselled on what to do during pregnancy and when giving birth. Women pregnant for less than three months are advised to start antenatal care at three months.
2	At 4 months of pregnancy	This is to affirm that the pregnant mother went for ANC. The pregnant women are encouraged to go for the second ANC visit. Pregnant women are educated on the advantages of exclusive breastfeeding of children until 6 months of age and continuous breastfeeding until they reach the age of 2. Advantages of giving birth in a health facility and hand washing will be highlighted during this visit.
3	At 6 months of pregnancy	Discuss the birth plan, timing and place of the birth, exploring potential challenges faced by expectant mothers in reaching the health facility and ways of overcoming these challenges. Expectant mothers are given information on the different family planning methods and where to go for services, and are encouraged to utilize one of the methods after delivery.
4	8 months of pregnancy	The mother is educated about the early signs of true labor, danger signs during labor will be explained to the households, as well as appropriate action to take in the case of these danger signs. The mother is also encouraged to deliver at a health facility and have some emergency money available. This is also the visit at which the mother needs to have a clean birthing kit available (the “Mama Kit” [23]).
5–7	The newborn period	This visit is done three times in the first week after birth, on Days 1, 3 and 7. The VHT ensures that exclusive breastfeeding and essential maternal and newborn care are not only understood but also practiced. Mothers are educated on the need to seek health care if the neonate develops fever and/or a cough, and the need to go for routine growth monitoring and immunization.

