No	Variable	Description of Variable	Tool to Be Used
Dependent Variables			
1	Appropriate pregnancy weight gain at end of months pregnancy	Pregnancy weight gain of 11.5 kg to 16 kg by the end of the pregnancy	SQ
2	Newborn morbidity within the first 28 days of life	Newborn morbidity (focusing on cord infections, sepsis, asphyxia, fever, common flu and cold and diarrhea, pneumonia) within the first 28 days of life	SQ and ttCR
3	Appropriate birth weight	Appropriate birth weight of 2.5 kg or more	SQ
4	Mortality of newborns and mothers	If the mother died during pregnancy or childbirth, if the baby died either during pregnancy, childbirth or within the first 28 days of life.	SQ and ttCR
5	Overall maternal wellness	During pregnancy or newborn period, a mother does not develop sepsis, urinary tract infections, obstruction during birth or any danger signs during this period.	SQ and ttCR
Independent Variables			
1	Uptake of timely goal-oriented ANC	With a focus on the recommended four visits, the associated recommended services offered during these visits and timeliness of attendance.	VHTR, SQ and ttCR
2	Clean birthing practices	Birth attended by a skilled health provider, delivery happened in a health facility and a mama kit was used during the process.	SQ and ttCR
3	Essential newborn care practices (ENC) during the newborn period	Early initiation of breastfeeding, cord care practices, baby thermal care, sustained breastfeeding and baby WASH practices.	SQ and ttCR
4	Positive male involvement in pregnancy and newborn care	Man participates in at least one ANC, does an HIV test with the mother, available during birth, supports mother to help her rest, contributes finances for related logistics.	SQ

Notes: SQ: Study questionnaire, ttCR: ttC register, VHTR: Ugandan VHT household register.

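### The maternal death outcome stops at childbirth although women are followed to six weeks after delivery, so postpartum deaths fall outside the mortality variable

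*Protocol article*

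**What the plan says.** Table 4, dependent variable 4, covers deaths of newborns and mothers. For the mother the condition is "If the mother died during pregnancy or childbirth". For the baby it is "if the baby died either during pregnancy, childbirth or within the first 28 days of life". Dependent variable 5, maternal wellness, begins "During pregnancy or newborn period, a mother does not develop sepsis", so its window extends past the birth.

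On follow-up, Section 2.4 states "The study will follow these participants from pregnancy until six weeks post-delivery", and the Abstract has participants "monitored throughout their pregnancy up to at least six weeks after delivery".

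On the intervention, Section 2.6 says "our focus is on the value of the four visits made during pregnancy, the three visits made when the child is in the newborn period", and adds "a fourth visit at six weeks to enhance exclusive breastfeeding and routine immunization". Table 1 places visits 5 to 7 on Days 1, 3 and 7 after birth and says of them: "The VHT ensures that exclusive breastfeeding and essential maternal and newborn care are not only understood but also practiced".

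Section 2.9 requires 1218 participants to complete the interventions and replaces anyone who drops out before six weeks after the birth. It does not mention deaths.

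**The concern.** The mother's mortality window is shorter than every related window in the plan. It ends at childbirth, while her follow-up, her illness outcome and her baby's mortality outcome all continue. A postpartum infection would count against the mother under variable 5, yet a death from it would not count under variable 4.

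This is a stated outcome definition, not a detail left to another document, and nothing elsewhere in the article widens it. If it is followed literally, the study will under-report the most serious maternal event during weeks in which it is already observing the women. Maternal mortality is also part of the study's rationale: the Abstract opens with it, and Section 2.2 gives Hoima's high rate as the reason for placing the intervention there.

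**Working it through.** **1. Can childbirth be read to include the weeks after it?** No. Within the same row the baby's window lists pregnancy, childbirth and the first 28 days as three separate periods. The third is given to the baby and not to the mother.

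**2. The windows side by side**

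| Item | Place | Ends at |
|---|---|---|
| Maternal death | Table 4, variable 4 | childbirth |
| Baby's death | Table 4, variable 4 | day 28 |
| Maternal wellness | Table 4, variable 5 | newborn period |
| Follow-up of women | Section 2.4; Abstract | six weeks (Abstract: at least six) |
| Last ttC visit studied | Section 2.6; Table 1 | six weeks |

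**3. Visits after delivery.** Section 2.6 and Table 1 give 4 in pregnancy + 3 in the first week + 1 at six weeks = 8 visits. After delivery: 3 + 1 = 4, and 4/8 = 50%.

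**4. Group size, reproduced from Section 2.8.** 1107 × 1.10 = 1217.7, rounded to 1218; 1218/2 = 609 per group.

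**5. Deaths affected.** Inputs: 336 per 100,000 live births (Section 1, national figure for 2016) and 609 women per group. Assumptions: one live birth per woman, and a national figure that includes deaths after delivery.

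- Expected per group: 609 × 336/100,000 = 2.05. In both groups: 1218 × 336/100,000 = 4.09.
- The share after delivery is not in the article. Assumed range: 25% to 60%.
- Uncounted per group: 2.05 × 0.25 = 0.5 to 2.05 × 0.60 = 1.2.
- Uncounted in total: 4.09 × 0.25 = 1.0 to 4.09 × 0.60 = 2.5.

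**6. Does a test depend on it?** Take a halving of maternal mortality as an illustrative effect, with n = 609 per group, two-sided 5%, clustering ignored. Power ≈ Φ(|p1 − p2|/SE − 1.96), where SE = √{[p1(1 − p1) + p2(1 − p2)]/n}.

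- Full window: p1 = 0.00336, p2 = 0.00168, SE = 0.00287. Power = Φ(0.585 − 1.96) = 8.4%.
- 25% left out: p1 = 0.00252, p2 = 0.00126, SE = 0.00249. Power = Φ(0.506 − 1.96) = 7.3%.
- 60% left out: p1 = 0.001344, p2 = 0.000672, SE = 0.00182. Power = Φ(0.370 − 1.96) = 5.6%.

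Maternal death is a descriptive outcome under either window.

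**7. Interaction with replacement.** A woman who dies on day 5 has not died under variable 4 and has not completed the interventions as Section 2.9 requires. That section does not say whether she counts as a drop-out, so replacing her is open on the text.

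**The case against.** The strongest reply is that little depends on this. The sample size targets a 10-point difference, with service uptake and newborn care as the focus. The deaths affected number about one per group, and the share after delivery is assumed. That stands, and it limits the point to the accuracy of the reported count and the consistency of the plan.

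Four stronger readings are tempting, and the article does not support them.

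- *The postpartum death disappears from the study.* Table 4 gives a one-line definition. The questionnaire and register are not shown and may record the death. A preceding sepsis or danger sign would count under variable 5. What is lost is the death in variable 4.
- *Row 4 pools maternal, fetal and newborn deaths into one endpoint.* It lists one condition for the mother and one for the baby, and does not say they are combined or share a denominator. Separate reporting lines would be a preference, not a correction.
- *Maternal deaths do not belong because the hypothesis concerns newborn survival.* Section 1 hypothesises an effect on pregnancy outcomes as well as newborn survival, and Section 2.5 names both.
- *Half the intervention is aimed at preventing postpartum maternal death.* The count of four in eight is right, but Section 2.6 describes the postnatal visits mainly in terms of newborn care, breastfeeding and immunization. Maternal care is one element of visits 5 to 7.

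Two qualifications also stand. Follow-up to six weeks is the plan, but Section 2.4 discontinues women who migrate. Migration is also the only discontinuation that section names, so replacing a woman who died is a possibility that Section 2.9 leaves open, not a stated rule.

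**Conclusion.** The point holds as an inconsistency in a stated outcome definition, and it is minor. Read literally, variable 4 leaves out maternal deaths after delivery that fall within planned follow-up, and Section 2.9 does not prevent those women from being replaced.

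The size is about 0.5 to 1.2 uncounted deaths per group out of 2.05 expected. This rests on the national ratio, one live birth per woman, and an assumed 25% to 60% share after delivery. The expected number would be higher if Hoima's rate exceeds the national one, as Section 2.2 suggests. The sample size does not change, and with power of roughly 6% to 8% under any of these windows, no test conclusion would plausibly turn on the definition.

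**What to change.** 1. In Table 4, variable 4, define maternal death as death during pregnancy, childbirth or up to six weeks after delivery. Leave the baby's window as it is.
2. In Section 2.9, state that the death of a mother is an outcome, that she stays in the sample, and that she is not a drop-out to be replaced.

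The cost is two short text changes. No contacts are added: follow-up already runs to six weeks, and Table 2 has control-district VHT visits around day 6 and around six weeks. One check is needed. The ttC register is an additional tool for the intervention area, so of the two sources Table 4 lists for variable 4, only the study questionnaire serves both districts. Confirm that it captures a mother's death up to six weeks in each.

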The Ugandan strategy [4] of implementing the VHT at the household level aims to promote the health and wellbeing of all village members. The coverage of each VHT is at least 30 households. The role of VHTs [12] includes the mobilization of village members for health activities mainly organized by the health centres in the area, keeping village health records up to date, making monthly village health reports and organizing meetings for the village members to provide an update on the current health status for that particular village. The VHT promotes health to prevent disease, reports village sickness to health workers, performs periodic checks for danger signs in village members who are sick, and focuses on maternal newborn and child health (MNCH) services affecting behavioral change.

Timed and targeted counselling (ttC) [13] is a package of key MNCH messages and actions that are disseminated and passed on to pregnant and breastfeeding mothers, aimed at achieving sustainable behavioural change at specific time points within the first 1000 days of a child’s life. The strategy also targets key decision makers in households (e.g., husbands, grandmothers). The approach addresses integrated MNCH needs of the target groups, barriers, and negotiation of agreements with household decision makers on issues affecting the women. Targeted pregnancy outcomes refer to timely goal-oriented ANC, birth preparedness, male involvement, and delivery at a health facility, which are considered as contributing to appropriate birth outcomes. Targeted outcomes are related to a newborn survival focus on the first 28 days of life: cord care practices, essential newborn care, male involvement, and immunization as a contribution to the growth and development of the baby. The current paper describes the protocol for a study examining whether the implementation of the ttC intervention improves pregnancy outcomes and newborn survival in rural Uganda. Our hypothesis is that ttC has a positive effect on both pregnancy outcomes and newborn survival.

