### 2.10. Sampling Procedure

A multi-stage sampling technique will be employed to select study participants. A total of 20 clusters of sub-counties will be selected and included in the study, based on the power calculation. Sub-counties with largest numbers of pregnant mothers registered by the VHTs will be included to ensure that the estimated study sample size is met. This will be used to increase the level of efficiency of sampling and each cluster will be considered as a sampling unit. At the beginning of the study, the team will consult the ttC registers from the VHTs in Hoima and the VHT registers from Masindi to assess the pregnancy registration per sub-county. For each sub-county, six villages will be randomly selected, with each village providing 10 households.

At the household, selection of pregnant mothers to be included in the study will be done systematically. In this probability sampling, participants will be selected from a larger population of pregnant mothers according to a random starting point and a fixed periodic interval. This periodic interval will be determined beforehand as two, which means that assuming the starting point is one as the first serial number on the VHT register, every pregnant mother with an even serial number will be selected to participate in the study, that is, 2, 4, 6, 8, etc. The sampling procedure is presented in Figure 3.

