8	When the baby is one month and 2 weeks	Malaria prevention is discussed here, as well as other illnesses, danger signs in the baby and immunization for the baby and hygiene practices. The VHT checks whether the child’s growth card has been plotted, gives support for exclusive breastfeeding, checks if the child has had its HIV confirmatory test as part of the prevention of mother-to-child transition of HIV program and whether the mother has any ideas about family planning methods.

**Table 2 mps-03-00073-t002:** Visits by VHTs to mothers during pregnancy or after childbirth in the control district as part of regular care.

Visit	Timing	Services Delivered by the VHTs
ANC	Pregnancy period	Ensuring that mothers actually attend ANC as early as required to acquire the initial goal-oriented services. Making the four visits to the household with a pregnant woman.
Newborn	Newborn (28 days)	Ensuring that the cord is healing, the baby is breastfeeding and that the initial immunization has been given to the child. Ensuring that the birth took place at the health facility and—if the birth happened at home—the VHT refers the mother and baby pair to the facility.
PNC	Postnatal period	Checking on the 6th hour that the health worker gives PNC. Visit the household around the 6th day and visit around 6 weeks after delivery to check whether the mother has plans of having the last PNC visit.
Immunization	Up to 9 months after birth	Conduct household mobilization visits to check on the completeness and preparedness for child immunization [26]. The Day 1 visit is for the VHT to check on the first day immunization. The VHT visits the household at around the 6th week after birth and then at around 10 weeks and 14 weeks after delivery.

**Table 3 mps-03-00073-t003:** Study period.

Study Period								
	Enrolment	Allocation	Post-Allocation					Close-Out
**TIMEPOINT**	Feb’19	Nov’19	Jan’20	Jun’20	Jan’21	Jun’21	Jan’22	Feb’22
Enrolment								
Eligibility screen	X	X	X	X	X			
Informed consent	X	X	X	X	X			X
Allocation		X	X	X	X	X		
Interventions								
[ttC implementation]			X	X	X	X	X	
[Control implementation]			X	X	X	X	X	
Assessments								
Baseline	X	X						
MTR Outcomes						X	X	
ETR Outcome								X

MTR outcome: Midterm review outcomes focusing on results from the ttC implementation alone. ETR outcome: End term review outcomes focusing on the comparison of ttC implementation and control intervention areas.

**Table 4 mps-03-00073-t004:** Study variables.

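### Overall maternal wellness fails on any danger sign, and ttC teaching and a Hoima-only register may make such signs better recorded in Hoima, biasing this outcome against ttC

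*Protocol article*

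**What the plan says.** Table 4, dependent variable 5 (overall maternal wellness), requires that during pregnancy or the newborn period "a mother does not develop sepsis, urinary tract infections, obstruction during birth or any danger signs during this period". Because of the last element, "any danger signs during this period", one danger sign is enough to fail. The listed tools are the study questionnaire and the ttC register.

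Table 1 describes what ttC adds:
- Visit 1 explains a list of pregnancy danger signs, and "the family is encouraged to notify the VHT in the case of any of these danger signs".
- At visit 4, "danger signs during labor will be explained to the households, as well as appropriate action to take in the case of these danger signs".

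Table 2 describes usual VHT visits in Masindi. Its rows cover antenatal attendance, newborn checks, postnatal care and immunization; the first begins "Ensuring that mothers actually attend ANC as early as required to acquire the initial goal-oriented services". No row mentions teaching households about danger signs or asking them to report any. The Background does say that a VHT in Uganda generally "performs periodic checks for danger signs in village members who are sick".

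On registers, the Abstract calls the ttC register an additional tool for the study area, and Section 2.10 says that "the team will consult the ttC registers from the VHTs in Hoima and the VHT registers from Masindi". Section 2.11 describes the ttC register as a record of day-to-day contact between household and VHT.

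**The concern.** The intervention can change how the outcome is detected as well as the outcome itself. A family that has been taught the signs and asked to report them is more likely to notice one and mention it. In Hoima there is also a running register in which it may be noted; in Masindi the only listed tool for this outcome is the end-of-intervention questionnaire. Every sign recorded only for these reasons turns a mother from well to not well in the intervention district.

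The error therefore runs against ttC. A true reduction in morbidity could be masked, and with no true effect the comparison could suggest harm. The adjustments in Section 3 for confounders and for clustering do not correct a difference between districts in how completely the outcome is recorded. Section 3.2 mentions recall bias where cards are missing, but not a difference in recognition between districts.

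**Working it through.** The plan gives no figure for this outcome, so there is none to reproduce. The check has two parts.

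**1. The two districts side by side**

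| Step | Hoima (ttC) | Masindi (usual care) |
|---|---|---|
| Pregnancy danger signs taught | Yes, visit 1 | Not listed in Table 2 |
| Family asked to notify the VHT | Yes, visit 1 | Not listed in Table 2 |
| Labour danger signs taught | Yes, visit 4 | Not listed in Table 2 |
| VHT checks of sick villagers | Yes, general VHT role | Yes, general VHT role |
| Study questionnaire | Yes | Yes |
| ttC register as a second source | Yes | No |

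Table 1 names no maternal danger signs in the newborn period: visits 5–7 name neonatal symptoms and visit 8 names danger signs in the baby. The mechanism is therefore clearest for pregnancy and labour.

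**2. Possible size, on assumed values**

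Let *p* be the true proportion of mothers with a danger sign and *r* the probability that a sign is recognised and recorded. Treating danger signs as the only component and ignoring false reports:

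- recorded wellness = 1 − *p* × *r*
- artefact with equal *p* in both districts = −*p* × (*r* in Hoima − *r* in Masindi)

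The documents give neither *p* nor *r*; all values here are assumptions.

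| True frequency *p* | Gap 10 points | Gap 20 points | Gap 40 points |
|---|---|---|---|
| 20% | −2 | −4 | −8 |
| 30% | −3 | −6 | −12 |
| 50% | −5 | −10 | −20 |

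Entries are percentage points of recorded wellness, Hoima minus Masindi. For example, at *p* = 0.30 with recognition of 70% against 50%, recorded signs are 0.30 × 0.70 = 0.21 and 0.30 × 0.50 = 0.15, an artefact of 6 points.

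Masking of a true benefit: suppose the true frequency is 40% in Masindi and 30% in Hoima.
- Recording 60% in both: 0.40 × 0.60 = 0.24 and 0.30 × 0.60 = 0.18, an apparent benefit of 6 points.
- Recording 60% in Masindi and 80% in Hoima: 0.40 × 0.60 = 0.24 and 0.30 × 0.80 = 0.24, no apparent difference.

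Chance of a misleading test: with no true difference, *p* = 0.30 and recording of 60% against 80%, recorded wellness is 0.82 in Masindi and 0.76 in Hoima. With 609 per group, the standard error is √[(0.82 × 0.18 + 0.76 × 0.24)/609] = 0.0233, and 0.06/0.0233 = 2.58. The probability of significance against ttC at two-sided 0.05 is about Φ(2.58 − 1.96) = 0.73. This ignores clustering, which would lower the probability but leave the bias unchanged.

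**The case against.** The case against runs as follows. Table 4 defines whether a mother develops a condition, not whether she reports it. The questionnaire is not shown; if it asks every mother about specific symptoms, dependence on prior teaching would be smaller. Table 2 is a summary, and control VHTs are trained, carry counselling cards and check sick villagers. Women in both districts need an antenatal card with a child health card, or a mother-child passport (Section 2.4). Only one of five dependent variables is at issue.

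Much of this stands, and it limits the claim. Three stronger readings may tempt a reader, and the documents do not support them:
- *Better recognition is bound to make Hoima look worse.* The net difference also depends on any true reduction in danger signs, on the unseen prompts and on some detection in Masindi. A worse result is a risk, not a certainty.
- *Both visits 1 and 4 ask families to report.* Only visit 1 does; visit 4 explains labour signs and what action to take.
- *The artefact can be measured against the planned 10% effect.* Section 2.8 does not tie that effect to maternal wellness, so the comparison carries little weight.

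What the objection does not remove is the difference in stated content and sources. Checking people who are already sick is not the same as teaching all pregnant households what to notice. And whatever the questionnaire asks, the second listed source is used in one district only.

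**Conclusion.** The point holds as a risk of differential ascertainment for this one outcome, directed against ttC. It rests on the stated definition, the stated content of visits 1 and 4, the absence of equivalent teaching from Table 2, and a register used only in Hoima. Its size cannot be determined from the documents: at an assumed true frequency of 30%, recognition gaps of 10 to 40 points give artefacts of 3 to 12 points, and smaller gaps give less. It is a worthwhile, inexpensive improvement and does not undermine the trial as a whole.

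**What to change.** For the district comparison:
- Take overall maternal wellness only from sources that both districts have: the questionnaire with the same symptom prompts, plus antenatal or child health cards. Keep the ttC register for the process evaluation and leave it out of this outcome.
- Report the named conditions (sepsis, urinary tract infection, obstructed birth) separately from any danger sign, and interpret the latter as partly a measure of recognition.
- State as a limitation that the named diagnoses may still be detected more often in Hoima if ttC raises facility contact.

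The cost is a revised row in Table 4 and a check that the questionnaire records the components separately with fixed prompts. That check can be made during the pre-testing still planned in Section 2.11; whether the present questionnaire already does this cannot be seen. The narrower composite will have fewer events. Common prompts reduce the effect of teaching on what mothers report but may not remove it, which is why the danger-sign component should be reported on its own.
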